---

### PROTOCOL SYNOPSIS

|                              |                                                                                                                                                                                                                                                                                                                                                                                                                                                                                                                                                                                                                                                                                                                                                                                                                    |
|------------------------------|--------------------------------------------------------------------------------------------------------------------------------------------------------------------------------------------------------------------------------------------------------------------------------------------------------------------------------------------------------------------------------------------------------------------------------------------------------------------------------------------------------------------------------------------------------------------------------------------------------------------------------------------------------------------------------------------------------------------------------------------------------------------------------------------------------------------|
| Title:                | Effect of Transcranial Direct Current Stimulation on Perioperative Anxiety in Patients undergoing Laparoscopic Colorectal Tumor Surgery: A Randomized Clinical Trial                                                                                                                                                                                                                                                                                                                                                                                                                                                                                                                                                                                                                                               |
| Study Type:           | A prospective, single-center, randomized, double-blind clinical trial                                                                                                                                                                                                                                                                                                                                                                                                                                                                                                                                                                                                                                                                                                                                              |
| Corresponding Author: | 
[name], Department of Anesthesiology, The Affiliated Hospital of Xuzhou Medical University, Xuzhou, China.
NMPA Key Laboratory for Research and Evaluation of Narcotic and Psychotropic Drugs & Jiangsu Province Key Laboratory of Anesthesiology & Jiangsu Province Key Laboratory of Anesthesia and Analgesia Application Technology, Xuzhou Medical University, Xuzhou 221004, Jiangsu, China.
 
[name], Department of Anesthesiology & Clinical Research Center for Anesthesia and Perioperative Medicine, The Fifth School of Clinical Medicine of Zhejiang Chinese Medical University    Huzhou Central Hospital    The Affiliated Huzhou Hospital, Zhejiang University School of Medicine    Affiliated Central Hospital Huzhou University, Huzhou 313003, Zhejiang, China.
 |

---

|                            |                                                                                                                         |
|----------------------------|-------------------------------------------------------------------------------------------------------------------------|
| Study Centers:      | The Affiliated Hospital of Xuzhou Medical University                                                                    |
| Ethics              | Approved by the Medical Ethics Committee of the Affiliated Hospital of Xuzhou Medical University
(XYFY2022-KL448-01) |
| Trial Registration: | www.chictr.org.cn Identifiers: ChiCTR2300068859                                                                         |

## I. STUDY OBJECTIVES

The experience of perioperative anxiety is prevalent among patients undergoing cancer surgery and often exerts a significant impact on the prognosis of surgical patients. The application of transcranial direct current stimulation (tDCS) has been reported to modulate cortical excitability and has demonstrated promising potential in the treatment of various anxiety-related disorders.

The objective of this study was to evaluate the efficacy of tDCS in reducing perioperative anxiety among patients undergoing laparoscopic colorectal tumor surgery.

## II. BACKGROUND

### A. Perioperative Anxiety

In this trial, anxiety is defining as an emotion characterized by feelings of tension, worried thoughts, and physical changes like increased blood pressure [1]. According to the Anxiety and Depression Association of America, around 40 million people in the United States have an anxiety disorder. It is the most common group of mental illnesses in the country. However, only 36.9% of people with an anxiety disorder receive treatment. Anxiety disorders are the most common of all mental disorders with 30% prevalence in the population, and they significantly contribute to the economic burden of disease.

---

Perioperative anxiety, which is one of the main psychological stresses experienced by patients who undergo surgery, can cause activation of the sympathetic nervous system and the hypothalamic–pituitary–adrenal [2].

The incidence of perioperative anxiety ranges from 11% to 80% in different disorders. Perioperative anxiety is associated with perioperative neurocognitive disorder, postoperative pain, and postoperative sleep disturbances, resulting in impaired quality of life and increased disease-related morbidity and mortality in patients [3].

## B. Dorsolateral Prefrontal Cortex and Amygdala

The dorsolateral prefrontal cortex (DLPFC) and amygdala play important roles in “emotion dysregulation” which has a profound impact on etiologic research of generalized anxiety disorder (GAD). The DLPFC regulates emotional processing, decision-making, and other high-level cognitive functions through extensive connections with other brain regions, and has been shown to play a key role in the pathophysiology of GAD [4]. Altered activation of the DLPFC in patients with GAD has been associated with emotional dysregulation and attention deficit. Anxiety states associated with acute stress can be considered to result from under-activation of the excitability level of the left DLPFC of the brain, as well as abnormalities in the work of the amygdala of the brain [5]. Additionally, functional abnormalities of the amygdala, known as the most prominent “fear-circuit” structure in the brain that plays a central role in automatic affective processing, have been found in most anxiety disorders [6]. The amygdala has also demonstrated responsibility for facilitating perceptual processing and bottom-up emotional control in individuals with GAD.

## C. Transcranial Direct Current Stimulation (tDCS)

The tDCS is a noninvasive brain stimulation modality that modulates cortical excitability through the application of weak, direct currents between two

---

electrodes placed on the scalp [7]. Studies have shown that tDCS can effectively rebalance the excitability levels between the two hemispheres by anodal stimulation over the left DLPFC and cathodal stimulation over the right DLPFC, thereby leading to the alleviation of anxiety [8].

### **III. METHODS**

This is a prospective, single-center, randomized, double-blind, controlled clinical trial conducted in the department of Anesthesiology at the Affiliated Hospital of Xuzhou Medical University from March to August 2023. The research protocol was approved by the Ethics Committee of the affiliated hospital of Xuzhou Medical University (XYFY2022-KL448-01). The trial was registered at the China Clinical Trial Center (<http://www.chictr.org.cn/>) with the registration identifier ChiCTR2300068859 on March 1, 2023. This report follows the Consolidated Standards of Reporting Trials (CONSORT) reporting guideline for randomized studies.

#### **A. Recruiting Methods**

On the day before the operation, potential participants are identified from the elective surgery list by a member of the research team. Patients aged 18 years or older who are scheduled to receive elective laparoscopic radical surgery for colorectal tumors with American Society of Anesthesiologists (ASA) physical status classification  $\leq$ III are screened to assess their study eligibility. Written informed consent is obtained from participants before enrolment in this trial.

#### **B. Inclusion Criteria**

Patients aged  $\geq$  18 years scheduled for elective laparoscopic radical surgery of colorectal tumors with ASA  $\leq$ III are eligible.

#### **C. Exclusion Criteria**

- 
1. Refuse to sign the test consent;
  2. Have neuropsychiatric diseases, and have a history of neurological or psychiatric diseases;
  3. There are craniocerebral or head injuries;
  4. Serious cardiovascular and cerebrovascular diseases;
  5. Those with metal implanted devices in the body;
  6. Mini-Mental State Examination score less than 15;
  7. Long-term use of psychotropic drugs such as cortisol or antidepressants and anxiety.

## D. Consent Procedure

All potential subjects who meet the inclusion criteria that are identified by the chief anesthetist and/or designee will be given the opportunity to participate. Participants or their legal surrogates will be given the consent/assent during the screening visit. They will be given the opportunity to review the consent/assent and ask questions about clarification on any aspects of the study. Any additional questions they have will also be answered by the investigator prior to signing the consent/assent. Once the consent/assent form is signed, a signed and dated copy of the authorization form will be provided to the subject and another copy will be placed in the participant's medical record at the Affiliated Hospital of Xuzhou Medical University.

## E. Randomization and Blinding

Based on the computer-generated random number table, participants are centrally randomized 1:1 to receive either active-tDCS group or sham-tDCS group. The allocation information is concealed in opaque envelopes and revealed until the investigators administer intervention to patients on the day before the surgery. Outcome assessors, the researchers who process data, other health care personnel, and patients are blinded to the treatment

---

allocation.

## F. Sample Size Calculation

All analyses are conducted with the intention-to-treat principle. Our preliminary data showed that the incidence of perioperative anxiety was 51.4%, and we assumed that a 40% reduction in the incidence of perioperative anxiety after two stimulation of tDCS would be considered a response to treatment. Using a study power of 0.80 and a significance level of 0.05, we then derived that 88 patients per group were required by using PASS 15.0. Considering a 10% loss of follow-up, we aimed to recruit 98 participants in each group.

## G. Statistical Analysis

Data analysis will perform in September 2023. The Kolmogorov-Smirnov test is used to assess normality, independent sample t-test is used if normally distributed data, and Mann-Whitney U test is used otherwise for non-normally distributed data. Continuous variables with normal distribution are represented by mean and standard deviation (SD), and variables with non-normal distribution are represented by median and interquartile range (IQR). Categorical variables are expressed as frequencies and proportions and analyzed using chi-square tests or Fisher exact tests.

Primary outcome is compared between the two groups using chi-square test or Fisher exact test, with differences between groups expressed as relative risk (RR) and 95% confidence interval (CI). The linear mixed-effects model is used to compare the secondary outcomes, with baseline (T0) values as covariates, treatment, time, and the interaction of time and treatment as fixed effects, and the subject's random intercept as a random effect to account for differences in time. The treatment-by-time interaction term is tested first. If significant, between- and within-treatment differences are tested for each time

---

point, and analyses are adjusted for multiple comparisons using the Bonferroni test for differences in within-treatment anxiety scores from baseline (T0). Otherwise, the main effect of treatment was tested next, and no Bonferroni correction was made for assessing the treatment effect at each time point. The difference and 95% confidence interval (CI) between medians were calculated with Hodges-Lehmann estimator. The relative risk (RR) and 95% CI were used to describe the differences in dichotomous outcomes. Data are analyzed using SPSS 25.0 (IBM Corp, Armonk NY) and hypothesis tests are two-sided at a level of 0.05.

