## J. Outcome measures

The primary outcome is the incidence of perioperative anxiety in patients from the day of surgery to 3 days after surgery after two sessions of tDCS intervention. Perioperative anxiety was measured using the Hospital Anxiety and Depression Scale-Anxiety (HADS-A) (**Appendix 1**). A HADS-A score of 8 or more is considered to be a patient experiencing anxiety. On the day before surgery, the researcher assesses the patient for anxiety in the ward treatment room (T0), followed by a second assessment of anxiety (T1) after the first tDCS intervention. On the day of surgery, the researcher conducted separate assessments before (T2) and after (T3) administering the second tDCS stimulus. Anxiety scores were assessed at two hours after surgery (T4), on the

---

first day after surgery (T5), the second day after surgery (T6), the third day after surgery (T7), and the third month after surgery (T8).

Secondary outcomes included anxiety scores (T1-T8), the incidence of postoperative delirium (POD, assessed by the Confusion Assessment Method [CAM] or Confusion Assessment Method intensive care unit [CAM-ICU] **[Appendix 2]** on the day of surgery and three days after surgery [T4-T7]); pain scores (assessed by the Numeric Rating Scale [NRS] **[Appendix 3]** at T4-T7); frail scores (assessed by the Fatigue, Resistance, Ambulation, Illness and Loss of Weight Index [FRAIL] **[Appendix 4]** at T5-T8); and sleep quality score (assessed by the Pittsburgh Sleep Quality Index [PSQI] **[Appendix 5]** at T4-T8).

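### The primary outcome is tested without adjustment for baseline HADS-A, although T0 is collected and already used as a covariate for the secondary outcomes

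*Protocol*

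**What the plan says.** Section G (Statistical Analysis) fixes the primary test: "Primary outcome is compared between the two groups using chi-square test or Fisher exact test". The effect measure is a relative risk with its interval. The section names no covariate for this comparison, and no adjusted or sensitivity analysis of the primary outcome is stated.

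Section J (Outcome measures) defines the event by a cut-off on one scale: "A HADS-A score of 8 or more is considered to be a patient experiencing anxiety". It also provides a pre-treatment measurement on that scale: "On the day before surgery, the researcher assesses the patient for anxiety in the ward treatment room (T0"). The first stimulation comes after this assessment.

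Section G treats T0 differently for the other outcomes: "The linear mixed-effects model is used to compare the secondary outcomes, with baseline (T0) values as covariates".

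Section B (Inclusion Criteria) admits adults "scheduled for elective laparoscopic radical surgery of colorectal tumors with ASA" III or lower, and sets no HADS-A limit. Section C excludes psychiatric history and long-term psychotropic use, but also sets no HADS-A limit. Section E describes 1:1 randomization from a computer-generated random number table and names no stratification factor.

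**The concern.** Patients with low and high anxiety at T0 are mixed in both arms, and some may already score 8 or more. T0 should predict later status: it is the same instrument, it is taken the day before the outcome window opens, and the form in Appendix 1 asks about the past week, so its recall period overlaps that of the later assessments. Neither the described randomization nor the primary analysis makes use of it.

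Two things are at stake. First, differences in starting anxiety that could be explained are left as noise, so the confidence interval for the RR is wider than it need be. Second, if one arm happens to start more anxious, part of that difference carries through to the primary RR, to a degree set by the T0–outcome correlation. If an imbalance then appears, an adjusted analysis added after unblinding would look data-driven, and readers would have two primary results with no prior rule for choosing between them.

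**Working it through.** **Inputs.** From section F: control incidence ("Our preliminary data showed that the incidence of perioperative anxiety was 51.4" per cent), a 40% relative reduction, power 0.80, alpha 0.05, 88 per group before loss and 98 after 10% loss. From section G: two-sided tests. Active-arm incidence is 0.514 × 0.6 = 0.3084, so the RR is 0.60 and the difference is 0.2056. The T0–outcome correlation ρ is not in the documents; it is assumed and shown as a range.

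**1. The plan's own figure.** With mean proportion (0.514 + 0.3084)/2 = 0.4112, the pooled formula is

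n = [1.96·√(2·0.4112·0.5888) + 0.8416·√(0.514·0.486 + 0.3084·0.6916)]² / 0.2056²
= (1.3639 + 0.5727)² / 0.04227 = 88.7, that is 89.

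The unpooled version gives 86. The stated 88 reproduces within the usual difference between formulas. Power by formula is 0.797 at 88 per group and 0.838 at 98. The trial is therefore sized for the unadjusted test.

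**2. Unadjusted precision.** SE(log RR) = √[0.486/(88·0.514) + 0.6916/(88·0.3084)] = √(0.01075 + 0.02548) = 0.190. Simulation gives 0.193.

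**3. The effect of adjusting, by simulation.** The outcome is a normal latent score with correlation ρ to baseline, cut so that the arms have incidence 0.514 and 0.3084. The comparison is chi-square against modified Poisson (log link, robust variance) with treatment and integer T0 HADS-A, at 88 per group, with 1,500 trials per ρ. The Monte Carlo error of a power near 81% is √(0.81·0.19/1500), about 1 point. The last two columns are taken relative to SE 0.193.

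| Assumed ρ | Power, chi-square | Power, adjusted | SE(log RR), adjusted | CI width on log scale | Variance |
|---|---|---|---|---|---|
| 0.3 | 80–81% | 81% | 0.188 | −3% | −5% |
| 0.5 | 80–81% | 85% | 0.180 | −7% | −13% |
| 0.6 | 80–81% | 87% | 0.176 | −9% | −17% |
| 0.7 | 80–81% | 89% | 0.169 | −12% | −23% |

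The RR is about 0.59–0.60 with or without adjustment, and type I error stays near 5%. At ρ = 0.5 the variance ratio (0.193/0.180)² = 1.15 means the adjusted analysis of 88 per group is about as precise as an unadjusted analysis of 88 × 1.15 = 101 per group.

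**4. Cross-check with another model.** Logistic regression on treatment and a continuous baseline, standardised to a marginal RR, with 4,000 trials per ρ at 88 per group:

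| Assumed ρ | Power, chi-square | Power, adjusted logistic | Variance of log RR, adjusted/unadjusted |
|---|---|---|---|
| 0 | 0.81 | 0.80 | 1.01 |
| 0.3 | 0.82 | 0.82 | 0.96 |
| 0.5 | 0.81 | 0.86 | 0.86 |
| 0.6 | 0.80 | 0.87 | 0.80 |
| 0.7 | 0.81 | 0.93 | 0.69 |
| 0.8 | 0.81 | 0.96 | 0.61 |

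The mean log RR is about −0.52 either way, so both analyses target the same RR. Under the null, rejection rates across the methods run from 0.044 to 0.058.

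**5. Chance imbalance.** The SE of the between-arm difference in mean baseline is √(2/88) = 0.15 SD. Take ρ = 0.6 and split an imbalance against the active arm evenly between the arms.

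- For 0.2 SD, each arm's latent mean moves by 0.6 × 0.1 = 0.06. Control: Φ(0.035 − 0.06) = 0.490. Active: Φ(−0.500 + 0.06) = 0.330. The expected unadjusted RR is 0.330/0.490 = 0.67 instead of 0.60.
- For one SE (0.15 SD), the same steps give about 0.65.

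**The case against.** The case on the other side is that nothing here is an error. In a 1:1 randomized trial an unadjusted chi-square with an RR keeps its type I error, the RR is unbiased over randomizations, its confidence interval already allows for chance imbalance, and the trial has its stated 80% power for this test. All of that stands, and it limits the point to efficiency.

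The size of the gain rests on a correlation the documents do not give; at 0.3 or below there is almost nothing to win. The simulations use a single later latent score, whereas section J counts anxiety over a window from the day of surgery to day 3, with surgery in between. How T0 relates to that windowed status is unknown. This stands too, and is why a range is shown. The logistic figures at ρ = 0.7 (93% power, 31% less variance) exceed those for modified Poisson (89%, 23%) and should not be credited to it.

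The imbalance example needs its scale kept in view: 0.2 SD is about 1.3 SE, with roughly a 9% chance of that much or more against the active arm. Adjustment also does not change the fact that patients already at 8 or more at T0 can count as events. That is a question of endpoint definition and adds no weight here.

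The planned mixed model for HADS-A scores adjusts for T0, but it concerns a secondary outcome and does not yield the primary RR. A separate analysis plan might add a supportive adjusted analysis, but the protocol itself names the primary test.

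**Conclusion.** The point holds as an avoidable loss of precision in the primary analysis. The planned test remains valid and the sample size adequate for it. At 88 per group, adjusting for T0 by modified Poisson raises power from about 80–81% to about 85–89%, and narrows the interval for the log RR by about 7–12%, if the T0–outcome correlation is 0.5 to 0.7. At 0.3 or below the benefit is negligible, but so is the statistical cost. The figures assume the section F incidences and a latent-normal outcome. A sizeable correlation is plausible, given the shared scale and short interval, but undocumented. The plan already accepts T0 as a covariate for the secondary outcomes and gives no reason for leaving it out of the primary comparison. The change should be made, though the trial's validity does not depend on it.

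**What to change.** In section G, make the primary analysis a modified Poisson regression (log link, robust variance) of HADS-A of 8 or more on treatment and T0 HADS-A score, with T0 as a continuous covariate. Report the adjusted RR, its two-sided 95% confidence interval and the p-value from that model. Keep the chi-square or Fisher exact test with the unadjusted RR as a supportive analysis. Logistic regression standardised to a marginal RR is an acceptable alternative; a logistic odds ratio alone is not, because it would change the stated effect measure.

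The text change is one sentence, the model is available in the planned software, and no new data or patients are needed; the 88 and 98 per group can stay. Because the trial is registered and ethics-approved, the change to the primary analysis should be documented as an amendment and fixed before unblinding.

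### For the secondary repeated-measures outcomes, Bonferroni is placed on within-arm changes from T0, while the between-arm tests at each time point stay uncorrected at 0.05

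*Protocol*

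**What the plan says.** Section G compares the secondary outcomes with a linear mixed-effects model. T0 is a covariate; treatment, time and their interaction are fixed effects; the only random effect is a subject intercept ("random intercept as a random effect to account for differences in time").

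The order of testing is set out: "The treatment-by-time interaction term is tested first." If it is significant, between-arm and within-arm differences are both tested at each time point, and Bonferroni is attached to one of the two sets: "analyses are adjusted for multiple comparisons using the Bonferroni test for differences in within-treatment anxiety scores from baseline (T0"). If it is not significant: "Otherwise, the main effect of treatment was tested next, and no Bonferroni correction was made for assessing the treatment effect at each time point." The general level is also fixed: "hypothesis tests are two-sided at a level of 0.05."

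Section J (Outcome measures) lists the time points: anxiety at T1-T8 (eight), pain at T4-T7 (four), FRAIL at T5-T8 (four) and PSQI at T4-T8 (five). The primary outcome, incidence of anxiety from the day of surgery to day 3, is compared by a single chi-square or Fisher test outside this model.

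**The concern.** The correction sits on the wrong comparisons. A change from T0 within one arm combines the effect of surgery, recovery, regression to the mean and, in the sham arm, response to sham. Randomisation does not protect it, and it cannot show a treatment effect. The between-arm difference at a given time is the randomised comparison, and no correction is named for it in either branch.

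The branch for a non-significant interaction adds to this. It names the main effect as the next test, then speaks of the treatment effect at each time point without correction. One reading is that the main-effect test replaces the per-time tests; the other is that uncorrected per-time tests follow anyway. The two readings have very different error rates.

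At stake is a chance difference at one visit being reported as a tDCS effect at that visit. T8 is the visit to watch: both stimulations are over by T3 and T8 is three months after surgery, so a false positive there would read as lasting benefit.

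**Working it through.** The plan states no familywise error rate, so there is no figure of its own to reproduce.

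**Inputs from the protocol.** Two-sided 0.05 per test (section G); eight anxiety time points (section J); 88 patients per group before the allowance for loss (section F).

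**Assumption.** The correlation between a patient's repeated scores is not given, so it is varied from 0 to 0.9, equal for all pairs of visits.

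**Independent tests, no gate.** 1 - (1 - 0.05)^8 = 1 - 0.95^8 = 33.7%.

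**Simulated test sequence.** 88 per arm, eight visits, complete data, a t-test at each visit, an F test of the interaction under equal correlation, and an F test of the main effect. The first three results columns assume no effect at any time. The last assumes a 0.8 SD effect at T1-T3 and counts errors over T4-T8 only; the interaction test then rejects in essentially every trial.

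| Correlation | Per-time tests always run | Only after significant interaction | After significant interaction or main effect | Effect at T1-T3 only: error over T4-T8 |
|---|---|---|---|---|
| 0 | 33.7% (exact) | 4.9% | 8.0% | 22.6% (exact) |
| 0.3 | 29.7% | 4.1% | 8.9% | 21.1% |
| 0.5 | 24.6% | 3.1% | 7.8% | 18.0% |
| 0.7 | 19.2% | 2.3% | 6.9% | 15.2% |
| 0.9 | 12.2% | 1.0% | 5.8% | 10.6% |

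The last column at correlation 0 is 1 - 0.95^5 = 22.6%. That is the ceiling for five tests with non-negative correlation; simulated values as high as 24% are sampling noise around it.

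**Where the errors arise.** At correlation 0.5, 21.5 of the 24.6 percentage points in the first results column come from trials with a non-significant interaction. The reading of the second branch therefore decides most of the size.

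**With Bonferroni on the eight between-arm tests.** The per-test level is 0.05/8 = 0.00625.
- Independent tests, no gate: 1 - 0.99375^8 = 4.9%. Simulated at correlations 0.3 to 0.9: 4.6% down to 2.0%.
- Early effect only, error over T4-T8: 2.9% down to 1.7% at correlations 0.3 to 0.9.

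**The gate itself.** A random intercept alone implies the same correlation between T2 and T3, on the same day, as between T1 and T8, about three months apart. Under assumed correlations that decay with time, or that set T8 apart, the interaction test at nominal 5% rejected in roughly 6-11% of trials with no effect.

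**The case against.** The strongest objection is that the plan has a gate. Per-time tests follow a significant interaction, and under the complete null that holds the error at 1.0-4.9%. This stands, and it means the 12-34% range is not a general property of the plan. It does not cure the defect. The gate protects only when there is no effect anywhere; once a real early effect opens it, the later time points have no protection. The second branch can also be read as bypassing it.

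It is also fair that the *Otherwise* sentence may mean only that one main-effect test replaces the per-time tests, so that no correction arises. The text does not settle this, so the finding there is ambiguity, not a stated intention to test.

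A reader might infer more than the protocol supports:
- *That the trial's main claim has an inflated error rate.* It does not. The primary outcome is one test at 0.05, and no secondary outcome is named as confirmatory.
- *That about one false positive is expected across all secondary time points* (8 + 4 + 4 + 5 = 21 tests, 21 × 0.05 = 1.05). This assumes every per-time test is always run, which ignores the gate.
- *That a false positive is likely.* Even with no gate and independent tests, the figure is 34%.
- *That change from T0 cannot be estimated because T0 is a covariate.* Section G does not say whether the response is the score or its change. With change as the response, the adjusted within-arm mean is available.

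Residual covariance is often left to a statistical analysis plan, so the random intercept is a secondary point here.

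**Conclusion.** The point holds for the secondary repeated-measures outcomes. As written, the multiplicity correction protects comparisons that carry no randomised evidence and leaves the between-arm per-time tests at 0.05. This is a rule the protocol fixes, not a detail it leaves open.

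The size depends on the reading and on a correlation the protocol does not give. For anxiety at T1-T8 it is about 12-34% if per-time tests run regardless of the interaction, about 6-9% if they follow a significant interaction or main effect, and at most about 5% under the complete null if the interaction gate is enforced and correlations are equal. With an effect at T1-T3 only, it is about 11-23% over the later time points. That illustration uses a large effect, 0.8 SD; a smaller one would open the gate less often.

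The random-intercept issue is secondary: the gate's own error is roughly 6-11% under assumed decaying correlations. The change should be made, but nothing here touches the primary analysis.

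**What to change.** In section G:

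1. Keep the interaction-first order.
2. Apply Holm or Bonferroni to the between-arm per-time tests, over each outcome's own time points: 0.05/8 = 0.00625 for anxiety, 0.05/4 = 0.0125 for pain and FRAIL, 0.05/5 = 0.01 for PSQI.
3. State that when the interaction is not significant, only the main effect of treatment is tested.
4. Report within-arm changes from T0 descriptively, without treatment claims. They need not be deleted.
5. Preferably, use a less restrictive residual covariance than the random intercept alone.

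Under equal correlation and no effect at any time, the chance of any false treatment claim on anxiety from this sequence is the main-effect part plus the corrected per-time part: 4.75% + 2.07% = 6.8% at correlation 0, falling to 4.79% + 0.21% = 5.0% at 0.9.

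The cost is wording, plus smaller p-values for single-time-point secondary claims; Holm loses less than Bonferroni. Testing the time-averaged effect first is not recommended as a required change: averaging over T1-T8 could dilute a short-lived effect, so it is a trade-off and not a correction.
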